| Pregnancy Test                                                      | X                              |                 |          |                 |          |          |          |          |                 |          |           |                        |                                    |                                     |
| PK testing                                                          |                                | X               |          | X               |          | X        |          |          | X               |          | X         |                        |                                    |                                     |
| COVID19 Health
and Wellbeing
Follow up
Survey
(Appendix 3)          |                                |                 |          |                 |          |          |          |          |                 |          |           | X                      | X                                  | X                                   |

1. Observations: Heart rate, temperature, oxygen saturations, blood pressure, respiratory rate
2. IMP should start to be administered within 24 hours of randomisation
3. Bloods/Nasopharyngeal swabs can be taken +/- 48 hours from scheduled time point unless otherwise specified. Screening bloods/NP swabs should be performed within 96 hours of randomisation
4. Nasopharyngeal swabs on day 1 should be taken as close to T0 (time of first drug administration) as possible
5. Patients discharged prior to day 15 should follow the outpatient schedule of assessments from point of discharge. Patients should return for clinic visit where possible, or be followed up by phone call if unable to attend

6. Follow-up visit at day 29 and 60 may be performed by telephone if patient is unable to attend clinic
7. Serum pregnancy test, for patients of child bearing potential only
8. Screening COVID-19 test can be done using any valid method of testing
9. PK Samples should be taken at the following times:

- Day 1: pre dose and 0.5 hours post dose
- Day 3: pre and 0.5 hours post dose
- Day 5: pre and 0.5 hours post dose
- Day 8: Pre dose
- Day 10: Pre dose

In addition, 16 volunteers (8 male, 8 female) will have more frequent sampling for PK on days 1 and 3 after either dose that day. Hours post dose: 0.5, 1, 2, 7, 12

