### **3.2 Eligibility criteria**

#### **Inclusion criteria**

1. Age 16 or over at time of consent
2. Exhibiting symptoms associated with COVID-19
3. Positive for SARS-CoV-2 on valid COVID-19 test
4. Point 2, 3, or 4 on the WHO COVID-19 ordinal severity scale at time of randomisation. (Symptomatic Independent, Symptomatic assistance needed, Hospitalized, with no oxygen therapy)
5. Have  $\geq 10\%$  risk of death should they be admitted to hospital as defined by the ISARIC4C risk index: <https://isaric4c.net/risk>
6. Able to provide written informed consent
7. Negative pregnancy test (women of childbearing potential\*)
8. Able to swallow oral medication

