### **Day 1-10^1**

WHO COVID 10 point ordinal severity scale assessment (daily – worst value in last 24 hours)

Documentation of concomitant medications (daily)

Assessment of adverse events (daily)

Routine observations/vital signs\* (daily)

Routine clinical blood tests: days 1,3,8,11 (+/- 48 hours)

Blood tests for immunological and epigenetic testing: days 1, 3 (+/- 48 hours)

Symptom directed clinical examination if clinically indicated

Administration of IMP (if applicable)

Nasopharyngeal swab (for SARS-CoV-2 PCR assessment and Viral Load): days 1 (at time of first dose), 3, 8, 10, 13 (+/- 48 hours)

Pharmacokinetic samples: according to the sample schedule (Appendix 5)

 Patients discharged during this time should follow the outpatient trial schedule. The timing of the first dose of favipiravir should be documented as Time zero (T0). The nasopharyngeal swab should be taken as close to this time as possible.

 On day 8, two swabs should be taken – one to be sent for immediate COVID-19 testing by any valid method, the other to be stored for later analysis of viral load.

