### **Day 1-10^1**

Dispensing of IMP (patients on favipiravir arm)  
WHO COVID 10 point ordinal severity scale assessment (daily – worst value in last 24 hours)  
Documentation of concomitant medications (daily)  
Assessment of adverse events (daily)  
Nasopharyngeal swab (for SARS-CoV-2 PCR assessment and viral load): day 8  
Administration of IMP and completion of Patient Diary (patients on favipiravir arm)

 Assessments on day 1-10 will be performed by telephone

 IMP may be dispensed in clinic following randomisation where possible, or couriered to the patient's home

 NP swab may be performed at home by the patient provided this is safe to do and safe transport to research laboratory has been arranged.

 Baseline PK sample can be taken at screening or pre-dose day 1. PK sampling will only be undertaken where sites can accommodate both pre and post dose sampling, and have the facilities to spin samples within 4 hours.

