### **5.7 Prohibited Therapy/Prohibited Medications/Permitted Concomitant Medications**

- Other medication taken for treatment of COVID-19 whether investigational or approved may be permitted on a case by case basis – please contact Sponsor & CI to discuss.
- When remdesivir is added to the UK protocols as part of the standard of care for treatment of COVID19, co-prescribing will be permitted with favipiravir with regular monitoring of LFTs according to the combined protocol schedules for both medications. remdesivir prescription must be recorded in the patient CRF.
- Dexamethasone has been shown to have benefit in the treatment of COVID-19 in certain groups of patients and is being adopted into standard care. Treatment with

dexamethasone is permitted concurrently with favipiravir. Coadministration of dexamethasone with favipiravir has not been studied. Dexamethasone is a substrate of CYP3A4 and a moderate inducer of this enzyme. Favipiravir does not appear to be metabolised by this pathway – but there is limited data and Investigators must be vigilant to the possibility of interactions. Dexamethasone prescription must be recorded in the patient CRF.

Details of the administration of any prohibited therapies will be collected on the trial CRFs and must be reported as a protocol deviation as per section 11.3.

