### **5.8 Dose Modifications for toxicity**

A subject should be removed from favipiravir treatment if one of the following criteria is met:

- AST or ALT > 5 x ULN
- ALT or AST > 3 x ULN AND total bilirubin > 2X ULN
- AST or ALT > 3 x ULN AND patient has right upper quadrant pain or eosinophilia
- Uric acid >20 mg/dL (1.2 mmol/l)
- Any other ≥ Grade 3 adverse event considered by the study team to be due to the trial drug.

Any > 3 x ULN AST or ALT event should be reported as a AE of Special Interest using the SAE form provided by the CRUK CTU Pharmacovigilance department.

No dose reductions are required for reductions in renal function if they occur during treatment. There no data for treatment with favipiravir during haemofiltration or dialysis – if this occurs during treatment the Sponsor & CI should be contacted to discuss the risk-benefit of continuing treatment for the individual case.

If remdesivir is administered in combination with favipiravir, EGFR must be >30ml/min and LFTs must be monitored daily during treatment with remdesivir. The stopping rules above for raised

transaminases apply for the combination treatment. Ensure remdesivir SmPC or equivalent source of information is consulted before initiating the combination treatment with favipiravir.

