#### **6.1.4 Reporting of a Serious Adverse Event**

Investigators must report all Serious Adverse Events (SAEs) to the Pharmacovigilance Office, CRUK CTU immediately and under no circumstances should this exceed 24 hours following first awareness of the event by the Investigator or site staff.

In addition, all incidences of AT (ALT or AST) elevation > 3 times upper limit of normal (ULN) are classed as adverse events of special interest and should be reported as SAEs within the timeframe stated above.

The following events are excluded from reporting as SAEs

- Elective hospitalisations
- Day case admissions for treatment of underlying disease
- A and E attendance for an event that is not immediately life threatening and does not result in admission

Serious Adverse Events occurring in the period between consent and randomisation do not require to be reported if they are unrelated to any study specific screening procedure.

SAEs can be reported via the following means:

Pharmacovigilance [contact]

Email: [[contact]](mailto:[contact])

For any guidance on SAE reporting please contact the Pharmacovigilance team on the following numbers:

[contact] or [name]

The purpose of this obligation is to ensure the CI on behalf of the Sponsor, has the necessary information to continuously assess the benefit-risk balance of the clinical trial.

For guidance on submitting and completing the initial and follow up SAE report forms please refer to the SAE report form Completion Guidelines, which will be provided by the Pharmacovigilance Office, CRUK CTU, Glasgow.

The CI will receive notification, by email, of all SAEs received.

SAEs must be reported locally by the PI at each site in accordance with the local practice at their site (i.e. R&D Office).

A follow-up report must be submitted when the SAE resolves, is unlikely to change, or as soon as additional information becomes available. If the SAE is a potential SUSAR then follow up information must be provided as quickly as possible and in the timeframe requested by the CRUK CTU and CI. All follow-up information is required to be reported promptly and follow up reports submitted until all AEs listed on the initial SAE report resolve. A follow-up report must be submitted if additional AEs listed on the initial SAE report have resolved or will never resolve. A follow-up report should also be submitted if additional AEs occur or new information becomes available about previously reported AEs.

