#### **7.1.5 Safety**

The worst toxicity grades (including AEs of special interest) experienced during active treatment will be compared between the study arms using the Mann-Whitney U test. P-values will be interpreted in the context of the multiple tests performed. This analysis will be restricted to events that occur in more than 10% of patients in either arm.

All Serious Adverse Events (including SARs and SUSARs) will be tabulated.

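### Minor: daily LFTs during remdesivir are required only with favipiravir (section 5.8), while section 7.1.5 compares worst grades between arms, so ALT/AST rises can be over-recorded on favipiravir if controls are tested less often

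*Protocol*

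**What the plan says.** **Testing rule.** Protocol section 5.8: "If remdesivir is administered in combination with favipiravir, EGFR must be >30ml/min and LFTs must be monitored daily during treatment with remdesivir". Section 5.7, on remdesivir entering UK standard care, also ties monitoring to the combination: "co-prescribing will be permitted with favipiravir with regular monitoring of LFTs according to the combined protocol schedules for both medications". Neither section, nor any other, states an LFT frequency for a control patient on remdesivir.

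**Common schedule.** The inpatient Schedule of Events has routine bloods on days 1, 3, 8 and 15 in both arms. Section 4.2.1 lists days 1, 3, 8 and 11. A footnote to the schedule adds "Bloods/Nasopharyngeal swabs can be taken +/- 48 hours from scheduled time point unless otherwise specified". Outpatients have no bloods between screening and day 15; section 4.2.2 states "Assessments on day 1-10 will be performed by telephone".

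**Event definition and comparison.** Section 6.1.4: "all incidences of AT (ALT or AST) elevation > 3 times upper limit of normal (ULN) are classed as adverse events of special interest". Section 7.1.5: "The worst toxicity grades (including AEs of special interest) experienced during active treatment will be compared between the study arms". The test is Mann-Whitney U. It is limited to events in more than 10% of patients in either arm, and its p-values are to be read in light of the number of tests.

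**The concern.** A patient's worst value cannot fall, and may rise, as more samples are taken. Section 5.8 makes the required number of samples depend on the arm, and section 7.1.5 compares the worst value between arms with no restriction to common sampling days. With otherwise equal testing, any resulting bias runs one way: towards more recorded ALT/AST elevations on favipiravir.

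Raised ALT and AST are among the favipiravir reactions listed in section 5.7.2, and they drive three of the stopping criteria in section 5.8. Readers will look for this laboratory signal, and a testing artefact could be mistaken for a drug effect or blur a real one.

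**Working it through.** The plan gives no figure to reproduce, so this is an illustration with no true difference between arms.

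**Inputs from the protocol:** 151 patients per arm (section 7.1); scheduled inpatient tests on days 1, 3, 8 (Schedule of Events), or 1, 3, 8, 11 (section 4.2.1); daily tests during remdesivir on favipiravir (section 5.8).

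**Assumed, because the protocol is silent:** a true risk of ALT/AST above 3 x ULN of 15% in both arms; remdesivir use of 30% (or 10%); a 5-day course starting on day r = 1 to 6; onset day s uniform over days 1-10 or days 3-10; duration L days; all patients on the inpatient schedule.

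**Detection rule.** An elevation is recorded if any of days s to s+L-1 is a test day. Controls have the scheduled days only. Favipiravir patients on remdesivir have these plus days r to r+4. The gap is the difference in detection probability.

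**Example** (L = 1, onset over days 3-10). Controls detect days 3 and 8: 2/8 = 0.25. On favipiravir with r = 1, detection is on days 3, 4, 5 and 8: 4/8, gap 0.25. With r = 2 it is 5/8, gap 0.375. With r = 3 to 6 it is 6/8, gap 0.50. The mean over start days is (0.25 + 0.375 + 4 x 0.50)/6 = 0.4375.

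**Gap, mean over r = 1 to 6 (range):**

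| L | Scheduled tests | Onset days 1-10 | Onset days 3-10 |
|---|---|---|---|
| 1 | with or without day 11 | 0.383 (0.30-0.40) | 0.438 (0.25-0.50) |
| 2 | 1, 3, 8 | 0.317 (0.20-0.40) | 0.396 (0.25-0.50) |
| 2 | 1, 3, 8, 11 | 0.300 (0.20-0.40) | 0.375 (0.25-0.50) |
| 3 | 1, 3, 8 | 0.250 (0.20-0.40) | 0.313 (0.25-0.50) |
| 3 | 1, 3, 8, 11 | 0.200 (0.20) | 0.250 (0.25) |
| 5 | 1, 3, 8 | 0.050 (0-0.20) | 0.063 (0-0.25) |
| 5 | 1, 3, 8, 11 | 0 | 0 |

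**Excess patients** = 0.15 x remdesivir share x gap x 151.

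- 30% use (6.795 x gap), L = 1 to 3: means from 6.795 x 0.200 = 1.4 to 6.795 x 0.4375 = 3.0. The worst alignment is 6.795 x 0.50 = 3.4, or 2.25 percentage points.
- 10% use (2.265 x gap), L = 1 to 3: means 0.45 to 1.0, worst 1.1.
- 30% use, L = 5 without day 11: means 0.3 to 0.4, worst 1.7. With day 11 it is 0.
- Controls on remdesivir also tested on days r, r+2 and r+4: the gap is exactly 0 for L = 2, 3 and 5. For L = 1 it is 0.10 to 0.25, or 0.7 to 1.7 patients at 30% use.

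**The 10% filter.** For L = 1 to 3, controls record 15% x 0.25 = 3.75% to 15% x 0.80 = 12.0% above 3 x ULN. The favipiravir arm at 30% use records 4.9% to 12.9%. The event may or may not qualify for the formal test.

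**Second check, on the test itself.** This simulated log(ALT/ULN) with mean -0.4, between-patient SD 0.5, within-patient SD 0.35 and day-to-day correlation 0.6. Grade cuts were 1, 3, 5 and 20 x ULN, all patients were tested on days 1, 3 and 8, and controls had no extra tests. Each setting used 1,000 simulated trials. With a 5-day course, the Mann-Whitney false-positive rate was about 4% at 10% use and 6% at 30%. With a 10-day course it was about 5% and 12%.

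**The case against.** **The case against.**

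- A sensitivity analysis on common visits is ordinary SAP content, and no sentence of the protocol is false.
- Closer monitoring of two drugs that both call for liver tests is proper.
- Section 5.7 speaks of schedules for both medications, which implies that remdesivir has a monitoring schedule of its own. Controls given it as standard care would be expected to follow that schedule.
- Section 6.1.4 requires every elevation above 3 x ULN to be reported in either arm, whatever test found it.
- Every input to the size is assumed. Remdesivir was only in prospect, and patients enter at "Point 2, 3, or 4 on the WHO COVID-19 ordinal severity scale at time of randomisation", without oxygen.
- Section 7.1.5 already has its 10% filter and its caution on multiple tests.

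**What stands.** The safety rule is sound and should stay. The size is small and conditional. Testing of controls may well be frequent in practice.

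**What does not stand.** This is not merely an omitted detail. The protocol itself fixes both the arm-dependent testing rule and the between-arm worst-grade comparison. Nor can low remdesivir use be taken for granted. The control-arm percentages assumed in section 7.1 put 11 + 5 + 7 + 5 + 13 + 13 = 54% on oxygen or worse, or dead, at day 15.

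**Stronger readings to avoid.** A reader might infer that controls on remdesivir are in fact tested less. The documents show only that the protocol does not require equal testing. A reader might also infer a seriously invalid test. In the simulation, false-positive rates of 11% to 60% appear only at 60% to 100% remdesivir use, and of 12% with a 10-day course at 30% use. Nothing in the protocol establishes such use or course length, and the simulation gives controls no extra tests.

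**Conclusion.** The point holds as a minor one. Required LFT frequency depends on the arm for patients on remdesivir, and a worst-grade comparison is sensitive to that.

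If controls on remdesivir are tested on scheduled days only, the excess averages about 1 to 3 recorded patients of 151. This rests on the assumed 15% risk, 30% use and 1 to 3 day elevations. At 10% use it averages 1 patient or fewer. It is zero for 5-day elevations with a day-11 sample, and for elevations of 2 days or more if controls on remdesivir are tested every other day. Earlier stopping of favipiravir, prompted by daily tests, may partly offset it in the grade comparison.

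The primary endpoint, the ordinal scale at day 15, does not use these tests and is not affected.

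**What to change.** Keep the daily monitoring in section 5.8, the special-interest reporting in section 6.1.4 and the all-results worst-grade comparison in section 7.1.5. Add to section 7.1.5:

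- A supportive between-arm ALT/AST comparison (grade, and above 3 x ULN) restricted to inpatient days 3 and 8, the scheduled on-treatment days common to both arms. Day 1 is close to baseline, and day 11 falls after the 10-day course.
- One sample per visit, the one nearest the nominal day. The 48-hour windows cover days 1-5 and 6-10, so without this rule every daily test would re-enter.
- A table of all ALT/AST results by arm and remdesivir use, with any difference interpreted from both analyses together.

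**Cost.** One extra analysis, with no extra bloods and no change to safety action. Section 5.7 already requires remdesivir to be recorded in the CRF. The added comparison covers only patients still in hospital on days 3 and 8, because discharged patients move to the outpatient schedule. It omits elevations seen only on unscheduled tests, but these remain in the all-results comparison, so no hepatic signal is lost.

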#### **5.8.1 Treatment Interruptions**

No planned treatment interruptions are permitted.

#### **5.8.2 Dose Modifications during Favipiravir Treatment**

No dose modifications once on treatment are permitted for toxicity. Please see instructions for stopping in section 6.8.

### **5.9 Participation in concurrent clinical trials**

Patients participating simultaneously in another clinical trial of investigational medicinal product (CTIMP) at the time of enrolment to GETAFIX may participate if the IMP in the other trial is not directly contraindicated in combination with favipiravir; it is not expected to interact with favipiravir based on available information and the Sponsor of the other CTIMP gives explicit permission and instruction for the withholding of the other IMP during participation in GETAFIX, if appropriate.

Patients will be permitted to take part in observational research at any time whilst participating in this trial.

Patients who have attained the primary trial end-point and are no longer receiving the trial intervention are permitted to enrol in other trials for COVID-19 subsequent to their participation in GETAFIX, subject to the inclusion criteria of those trials.

If a consideration is required that is not detailed above, the Principal Investigator seeking the consideration should seek approval from the Chief Investigator (CI) and Sponsor prior to enrolling the patient in either GETAFIX or the other trial. It is imperative that the Sponsor(s) of the both studies approve co-enrolment within their respective trials.

### **5.10 Duration of Trial Participation**

#### **5.10.1 Duration of Trial Treatment**

Treatment with favipiravir is for 10 days only unless the participant experiences unacceptable toxicity or the treating clinician and patient decide it is in the patient's best interest to stop treatment sooner.

#### **5.10.2 Duration of Trial Follow-up**

All randomised participants will be followed up until day 60.

## 6 SAFETY REPORTING

Safety reporting will be performed by the Pharmacovigilance Department of the CRUK CTU Glasgow as delegated by the trial Sponsor

### 6.1 Pharmacovigilance

#### 6.1.1 Definitions

| Term                               | Definition                                                                                                                                                                                                                                                                                                                                                                                                                                                                                                                                                                                                                                                                                                                                                                                                                                                                                                                                                                                                                                                                                                                                                                                                                                                                                                                                                                                                                                  |
|------------------------------------|---------------------------------------------------------------------------------------------------------------------------------------------------------------------------------------------------------------------------------------------------------------------------------------------------------------------------------------------------------------------------------------------------------------------------------------------------------------------------------------------------------------------------------------------------------------------------------------------------------------------------------------------------------------------------------------------------------------------------------------------------------------------------------------------------------------------------------------------------------------------------------------------------------------------------------------------------------------------------------------------------------------------------------------------------------------------------------------------------------------------------------------------------------------------------------------------------------------------------------------------------------------------------------------------------------------------------------------------------------------------------------------------------------------------------------------------|
| Adverse Event (AE)          | An adverse event (AE) is any untoward medical occurrence in a subject to whom a medicinal product is administered, which does not necessarily have a causal relationship with this treatment.                                                                                                                                                                                                                                                                                                                                                                                                                                                                                                                                                                                                                                                                                                                                                                                                                                                                                                                                                                                                                                                                                                                                                                                                                                               |
| Adverse Reaction (AR)       | An adverse reaction (AR) is any untoward and unintended occurrence in a subject to whom a medicinal product has been administered which is thought to be caused by or related to that product.                                                                                                                                                                                                                                                                                                                                                                                                                                                                                                                                                                                                                                                                                                                                                                                                                                                                                                                                                                                                                                                                                                                                                                                                                                              |
| Serious Adverse Event (SAE) | 
A serious adverse event (SAE) means any untoward medical occurrence that at any dose requires the following, whether or not considered related to the trial treatment.
 

• Requires inpatient hospitalisation or prolongation of existing hospitalisation*

• Results in persistent or significant disability or incapacity

• Results in a congenital anomaly/birth defect

• Is life threatening (i.e. at the time of the event)**

• Or results in death

• Is considered medically significant by the Investigator***

 
*Requires in-patient hospitalisation should be defined as a hospital admission required for treatment of an AE. No time frame is specified for the duration of the admission.
 
**Life threatening means that the patient was at immediate risk of death from the event as it occurred. It does not include an event that, had it occurred in a more serious form, might have caused death.
 
***Considered medically significant by the Investigator are events that may not result in death, are not life threatening, or do not require hospitalisation, but may be considered a serious adverse experience when, based upon appropriate medical judgement, the event may jeopardise the patient and may require medical or surgical intervention to prevent one of the outcomes listed above.
 |

| Term                                                          | Definition                                                                                                                                                                                                                                                                                                                                                                                                                                                                                                                                                                                                                                                                                                                                                                                                                                                                                                                                                                                                                                                                                                                                                                                                                                         |              |             |                  |                                                  |                 |                                                                                                                                                                                                                                                                                                          |                 |                                                                                                    |                   |                                                                                                                    |
|---------------------------------------------------------------|----------------------------------------------------------------------------------------------------------------------------------------------------------------------------------------------------------------------------------------------------------------------------------------------------------------------------------------------------------------------------------------------------------------------------------------------------------------------------------------------------------------------------------------------------------------------------------------------------------------------------------------------------------------------------------------------------------------------------------------------------------------------------------------------------------------------------------------------------------------------------------------------------------------------------------------------------------------------------------------------------------------------------------------------------------------------------------------------------------------------------------------------------------------------------------------------------------------------------------------------------|--------------|-------------|------------------|--------------------------------------------------|-----------------|----------------------------------------------------------------------------------------------------------------------------------------------------------------------------------------------------------------------------------------------------------------------------------------------------------|-----------------|----------------------------------------------------------------------------------------------------|-------------------|--------------------------------------------------------------------------------------------------------------------|
|                                                               | Medical and scientific judgement should be exercised in deciding whether an event is “serious” in accordance with this criterion                                                                                                                                                                                                                                                                                                                                                                                                                                                                                                                                                                                                                                                                                                                                                                                                                                                                                                                                                                                                                                                                                                                   |              |             |                  |                                                  |                 |                                                                                                                                                                                                                                                                                                          |                 |                                                                                                    |                   |                                                                                                                    |
| Serious Adverse Reaction (SAR)                         | 
A serious adverse reaction (SAR) is a SAE that may be related to trial treatment. The assessment of “relatedness” is primarily the responsibility of the Principal Investigator (PI) at site or agreed designee. SAEs will be considered related if the SAE is documented as possibly, probably or definitely related to protocol treatment. The assessment of relatedness is made using the following:
 
 
 Relationship	Description	
 
 Unrelated	There is no evidence of any causal relationship.	
 
 Possible	There is some evidence to suggest a causal relationship (e, g. the event occurs within a reasonable time after administration of the trial medication). However, the influence of other factors may have contributed to the event (e.g. the patient’s clinical condition, other concomitant treatments).	
 
 Probable	There is evidence to suggest a causal relationship and the influence of other factors is unlikely.	
 
 Definitely	There is clear evidence to suggest a causal relationship and other possible contributing factors can be ruled out.	
 
 | Relationship | Description | Unrelated | There is no evidence of any causal relationship. | Possible | There is some evidence to suggest a causal relationship (e, g. the event occurs within a reasonable time after administration of the trial medication). However, the influence of other factors may have contributed to the event (e.g. the patient’s clinical condition, other concomitant treatments). | Probable | There is evidence to suggest a causal relationship and the influence of other factors is unlikely. | Definitely | There is clear evidence to suggest a causal relationship and other possible contributing factors can be ruled out. |
| Relationship                                                  | Description                                                                                                                                                                                                                                                                                                                                                                                                                                                                                                                                                                                                                                                                                                                                                                                                                                                                                                                                                                                                                                                                                                                                                                                                                                        |              |             |                  |                                                  |                 |                                                                                                                                                                                                                                                                                                          |                 |                                                                                                    |                   |                                                                                                                    |
